### Design and setting

CaMISS-Prospective is an observational analytic prospective cohort study. All the patients have been consecutively selected between April 15, 2013 and May 20, 2015, from 13 hospitals in 4 Spanish regions (Andalusia, Canary Islands, Catalonia, and the Basque Country). All participant centers belongs to the Spanish National Services were primary care and hospital emergency departments are free. Regions and participating hospitals are listed in Table 2.

**Table 2 Tab2:** Patients recruited by area and hospital

Region	Hospital	Valid patients
Catalonia	Hospital del Mar, Barcelona	97
Basque Country	Hospital Galdakao-Usansolo, Bizkaia	197
	Hospital de Cruces, Bizkaia	246
	Hospital de Basurto, Bizkaia	125
	Hospital de Txagorritxu, Araba	229
	H.U. Donostia, San Sebastián, Gipuzkoa	245
	Instituto Oncológico, San Sebastian, Gipuzkoa	134
Andalusia	Hospital Costa del Sol, Malaga	80
	Antequera, Málaga	6
Canary Islands	Hospital Nuestra Sra de La Candelaria (Tenerife)	61
	Hospital Universitario de Canarias (Tenerife)	
	Complejo Materno-Insular (Gran Canaria)	36
	Clínica San Roque (Gran Canaria)	
Total		1456

### Study population

Women older than 18 years with an incident breast tumor will be included. The breast cancer diagnosis considered will be that reached after a biopsy of the tumor, including cases of ductal carcinoma in situ, invasive ductal carcinoma, tubular carcinoma, mucinous carcinoma, papillary carcinoma, cribriform carcinoma, invasive lobular carcinoma and lobular carcinoma in situ.

Symptomatic breast cancer will be included, as well as screened and interval breast cancer. The breast cancer screening program is public and universal in Spain. Following the recommendations of the European Guidelines for Quality Assurance in breast cancer screening and diagnosis [14], the Spanish Breast Cancer Screening Program provides free biennial screening to women who are between 50 and 69 years old. Recently, women aged from 45 to 49 years and 65 to 69 years are being incorporated into screening programs. Interval breast cancer is defined as primary breast cancer diagnosed in a woman who had a screening test, with or without further assessment, with a negative result, and diagnosed well before the next invitation to the screening test or before a period of time equal to the screening interval in a woman who has reached the upper age limit for screening [15].

Exclusion criteria are: diagnosis of sarcoma, lymphoma or inflammatory carcinoma; breast cancer recurrence; terminal illness; and a severe mental or physical condition or any other factor which interferes with the woman’s ability to complete the questionnaires. In addition, in situ carcinomas will be excluded from the survival analysis.

Socio-demographic and clinical data will be collected on women lost to follow-up. Figure 1 represents flow-chart of the recruitment and Table 2 represents data collection in participant centers.

**Fig. 1 Fig1:**
[figure not shown]
Flow chart

### Information and data collection

Eligible patients are to be selected from the surgery lists if surgery is indicated or, when neoadjuvant therapy is the first treatment given, from the lists for oncological treatment. Patients are contacted by phone and informed of the study objectives and, if they agree to participate, asked to provide written informed consent.

Our goal is to follow-up participants for 5 years from the confirmation biopsy. Figure 2 summarizes the data collection process. Clinical and personal data will retrieved from medical records by trained reviewers before admission, and at 2 and 5 years after diagnosis. Information on hospital characteristics has been provided by the management of each hospital. In order to collect data on health-related quality of life, patients will be contacted to complete questionnaires administered by trained interviewers after their first treatment and at 2 years. The first interview is to be performed in the period between diagnosis and the date of surgery or the beginning of the neoadjuvant therapy in the cases in which this therapy is the first option. At 2 years, patient-reported outcomes will be self-reported by mail or through self-administered questionnaires completed during a follow-up visit. To increase the response rate up to three reminders will be sent: at 2 weeks and at 2 months after the first contact. In the interval, non-responders will be also telephoned to remind them that a questionnaire has been sent and also to offer them the option to respond over the phone if they prefer. If funding is available, the same procedure will be carried out at 5 years.

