**Methods:**

Prospective cohort study involving 13 hospitals in Spain with a follow-up period of up to 5 years after diagnostic biopsy. Eligibility criteria: Patients diagnosed with breast cancer between April 2013 and May 2015 that have consented to participate in the study. Data collection: Data will be collected on the following: pre-intervention medical history, biological, clinical, and sociodemographic characteristics, mode of cancer detection, hospital admission, treatment, and outcomes up to 5 years after initial treatment. Questionnaires about quality of life (EuroQoL EQ-5D-5 L, the European Organization For Research And Treatment Of Cancer Core Quality Of Life Questionnaire EORTC QLQ-C30 join to the specific breast cancer module (QLQ-BR23), as well as Hospital Anxiety and Depression Scale were completed by the patients before the beginning of the initial treatment and at the end of follow-up period, 2 years later. The end-points of the study were changes in health-related quality of life, recurrence, complications and readmissions at 2 and 5 years after initial treatment. Statistical analysis: Descriptive statistics will be calculated and multivariate models will be used where appropriate to adjust for potential confounders. In order to create and validate a prediction model, split validation and bootstrapping will be performed. Cost analysis will be carried out from the perspective of a national health system.

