## Methods/Design

### Aim

The specific study objectives (which are set out in detail in Table 1) are, in brief: 1. to assess outcomes related to a) process of care (early diagnosis, access to health care and screening programs, delays in diagnosis, and variability in treatments), and b) patients (sociodemographic and clinical characteristics, including biomarkers, and patient-reported outcomes, such as quality of life and emotional state); 2. to create and validate prediction models (for changes in quality of life, relapse and death); and 3. to assess the costs associated with breast cancer care and its potential variations between Spanish regions.

**Table 1 Tab1:** Objectives

1. Outcomes assessment	2. Creation of predictive models	3. Health services evaluation in breast cancer patients in Spain
To describe and analyse variability in outcomes by mode of detection, hospital, region and surgeon	• To create and validate predictive rules for relapse, mortality and complications	• To estimate the average costs of breast cancer care in Spain
To describe and analyse variability in the diagnostic process and treatment	• To identify risk factors for poor health-related quality of life 2 years after treatment	• To investigate differences between Spanish regions
To explore potential inequalities by age, education and socioeconomic level	• To validate our predictive rules for relapse, mortality and complications in a retrospective sample of patients from early detection programs	• To identify the most efficient process and treatments in breast cancer
To evaluate the impact of first hospital care (urgent or scheduled) and of delays on relapse, metastasis and death		

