### Complications

A checklist (yes/no) is used for complications throughout the course of the follow-up period (intra-surgical, during hospital admission, and up to 2 and 5 years after the intervention, including complications related to reconstructive surgery). When there is no information on complications in the medical record, it will be assumed that none occurred.

Surgical severity: We record the use of the following surgical techniques (ranked from least to most complex): conservative surgery (tumorectomy, quadrantectomy, and segmentectomy), simple mastectomy, radical mastectomy, modified radical mastectomy, skin-sparing mastectomy, nipple-sparing mastectomy, areola-sparing mastectomy, breast reconstruction and contralateral prophylactic mastectomy.

pTNM: Staging is performed following the American Joint Committee on Cancer [27, 28], being pTNM considered except for cases who received neoadyuvant therapy (cTNM).When there are no pTNM staging data, the analogous cTNM will be used, otherwise, missing value will be recorded. In cases of bilateral cancer, we will consider the final stage as a peak between right and left breast. In the cases of Tx, Nx or Mx, we will consider the disease to be T0, N0 or M0. If cM is missing, then cM will be considered to be 0.

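### Record review is timed from diagnosis but the 2- and 5-year end-points run from treatment or intervention, so late-treated women are observed for less than the stated window

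*Protocol article*

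**What the plan says.** The protocol article uses these reference dates.

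- **Biopsy or diagnosis.** The Abstract describes a cohort "with a follow-up period of up to 5 years after diagnostic biopsy". Information and data collection repeats this: "Our goal is to follow-up participants for 5 years from the confirmation biopsy". The same section has records reviewed "by trained reviewers before admission, and at 2 and 5 years after diagnosis". The cost analysis also starts at diagnosis, with 24- and 60-month periods.
- **Initial treatment.** The Abstract's end-points, besides quality of life, are "recurrence, complications and readmissions at 2 and 5 years after initial treatment".
- **Intervention.** The Complications section applies its checklist "intra-surgical, during hospital admission, and up to 2 and 5 years after the intervention".

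Table 1 lists an objective on the impact "of delays on relapse, metastasis and death". The Variables section records three delays: symptoms to first contact, first appointment to histological diagnosis, and diagnosis to treatment. It also lists the dates of diagnosis, surgery and treatments. Recurrence is defined as cancer returning after a period in which none was detected. Women enter through treatment lists: "Eligible patients are to be selected from the surgery lists if surgery is indicated", or from the oncology lists when neoadjuvant therapy comes first.

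**The concern.** Medical records are the source for relapse, complications and readmissions. If the 2-year review is done as written, a woman treated *d* months after diagnosis has only 24 − *d* months of post-treatment record against a stated 24-month end-point. Duration of the project makes the 5-year stage depend on funding, so a later review cannot be relied on to fill the gap.

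The missing time is not random, because *d* is an exposure under Table 1. Recurrence needs a preceding cancer-free period, so months before treatment carry essentially no relapse risk. On a diagnosis clock, longer delay therefore means less time in which relapse can be recorded. The Statistical analysis section names logistic regression for dichotomous outcomes, including relapse, and that model has no term for time at risk. Two analysts following different sections could also report different 2-year rates for the same women.

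**Working it through.** **The plan's own figures.** Sample size calculation asks for 100 events at a 7% two-year relapse rate: 100 / 0.07 = 1429, close to the 1456 analysed. The observed rate is 4%: 1456 × 0.04 = 58.2 events, and 58.2 / 10 = 5.8, the stated six predictors. These do not depend on the time origin, but they supply the two relapse rates used below.

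**Assumptions.** Constant relapse hazard *h* after treatment; no relapse before treatment; no true effect of delay. The documents give no delay distribution, so delays of 1, 2, 3 and 6 months are assumed.

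**Formulas.** With relapse risk R at 24 months, h = −ln(1 − R)/24. If the window closes H months after diagnosis, time at risk is H − d, and risk = 1 − exp(−h(H − d)). The odds ratio against d = 0 is [exp(h(H − d)) − 1] / [exp(hH) − 1].

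For R = 4%, h = 0.04082/24 = 0.001701 per month. Example, d = 6, H = 24: risk = 1 − exp(−0.001701 × 18) = 3.02%; odds ratio = 0.03109/0.04167 = 0.746.

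| Delay (months) | Share of 24 months lost | 24-month risk (R = 4%) | Odds ratio at 24 months, R = 4% / 7% | Odds ratio at 60 months, R = 4% / 7% |
|---|---|---|---|---|
| 0 | 0 | 4.00% | 1 / 1 | 1 / 1 |
| 1 | 4.2% | 3.84% | 0.958 / 0.957 | 0.982 / 0.982 |
| 2 | 8.3% | 3.67% | 0.915 / 0.914 | 0.965 / 0.964 |
| 3 | 12.5% | 3.51% | 0.873 / 0.871 | 0.948 / 0.946 |
| 6 | 25% | 3.02% | 0.746 / 0.743 | 0.895 / 0.892 |

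**Effect on a test.** Split 1456 women into two groups of 728, R = 4%, H = 24. With p̄ the mean of the two risks, the standard error is √(2p̄(1 − p̄)/728), *s* is the risk difference divided by it, and the two-sided rejection rate is 1 − Φ(1.96 − s) + Φ(−1.96 − s).

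- 3 months against 1 month: 3.51% against 3.84%, 2.4 fewer events, s = 0.33, rejection about 6% instead of 5%.
- 6 months against 1 month: 3.02% against 3.84%, 6.0 fewer events, s = 0.86, rejection about 14%.

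**After the fix.** If every woman has the same 24 or 60 months from the date at which relapse becomes possible, time at risk no longer depends on *d* and the odds ratio is 1 under no effect.

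**The case against.** The strongest reply is that the biopsy date sets only the length of follow-up and the timing of record retrieval. The sentence that defines the end-points already dates them from initial treatment. The intervention date appears only for the complications checklist, and for women operated on first it is the same as initial treatment. The dates needed for a single origin are collected, and Study population mentions a survival analysis. Logistic regression is named for the prediction models; no section says which model or origin serves the delay objective. An article may leave that choice to the analysis plan.

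Much of this stands, and it rules out some stronger readings.

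- **A reader might infer that the delay objective is biased as planned.** The documents do not show that. The bias arises only if a fixed window from diagnosis is analysed without person-time.
- **A reader might extend it to all delays and outcomes.** The other two delays end at or before histological diagnosis, so choosing biopsy or treatment as origin does not change time at risk with them. Complications are not among the delay objective's outcomes. The protocol's definition of metastasis needs no cancer-free interval. Death can occur from diagnosis onward; there the only concern is that a woman must reach a surgery or oncology list to enter.
- **A reader might use neoadjuvant women to size the effect.** Surgery at 6, 7 or 9 months against 1 month gives risk ratios of 0.79, 0.74 and 0.66. For these women neoadjuvant therapy is the first treatment, so the contrast reflects treatment sequence, not delay to treatment. A first-treatment origin would barely change it: 19, 18 or 16 months at risk against 24 gives about 0.80, 0.75 and 0.67.

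What the reply does not answer is the data-collection gap. A review closing 24 months after diagnosis cannot supply a 24-month post-treatment end-point for a woman treated late, whatever model is chosen.

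**Conclusion.** The concern holds in a limited form. The stated reference dates conflict, and a 2-year review done as written leaves the treatment-based end-points incompletely observed by exactly the diagnosis-to-treatment delay. Whether this biases the delay objective depends on an analysis choice that the article does not state.

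If relapse is taken as yes/no in a window fixed from diagnosis, the error favours longer delay. Its size at 2 years is an odds ratio of about 0.96 to 0.87 for delays of 1 to 3 months and 0.75 for 6 months. At 5 years it is 0.98 to 0.90 (0.89 with a 7% two-year rate). It is therefore minor for short delays and material only near 6 months. These figures rest on a constant hazard, no relapse before treatment, and assumed delays. The point is worth correcting because it changes which events are counted and the correction is cheap.

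**What to change.** 1. State one time zero per end-point and use it in every section: treatment-based for relapse, complications and readmissions, as the Abstract already has it, and diagnosis for costs, as the cost analysis has it.
2. Time the 2-year record review, or extend the extraction, so that it covers 24 full months from that date for every woman.
3. For the diagnosis-to-treatment delay, start follow-up at first treatment with the delay as a baseline exposure, and use time-to-event methods or equal windows.
4. For women given neoadjuvant therapy, if relapse is counted only after surgery or a documented cancer-free date, make that date the single relapse origin and run the window from it.
5. If death is counted from diagnosis, let women enter the risk set when they are listed or consent.

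The cost is protocol wording, date arithmetic on dates already collected, and a somewhat later record review for women treated late.

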**Fig. 2 Fig2:**
[figure not shown]
Data Collection process

### Variables

Reviewers in each hospital were provided with a handbook with instructions to follow in the data collection process.-Exposure variables:*Related to the patients’ personal background*: date of birth, sociodemographic variables (level of education, occupation of the patient or of the head of the household, marital status and living arrangements), height, weight, lifestyle habits, gynecological history (family history of gynecological cancer, oral contraceptives or hormonal replacement therapy, first and last menstruation date, menopausal status [pre- or postmenopausal], number of pregnancies and of births, breastfeeding [yes/no and duration]); and comorbidities (Charlson Comorbidity index) [16].*Related to the hospital*: number of beds, whether it is a teaching hospital, catchment population size, number of patients treated for breast cancer annually, and whether it has a breast cancer unit and medical or radiation oncology services.*Related to the process of care*: date of first contact with medical care (scheduled/emergency), time between the first symptoms and the first contact with medical services, time between the first medical appointment and histological diagnosis, time between diagnosis and treatment, and date of diagnosis.*Related to the pre-intervention tumor history*: mode of detection (symptomatic, screen-detected), symptoms (lump, lymph nodule, swelling or hardening of a part of breast, change in the size or shape of the breast, skin retraction, ulceration/wound, pain, secretion, inflammation, nipple retraction), date of the first symptom, clinical TNM classification (cTNM), additional diagnostic tests (ultrasound scan, magnetic resonance imaging [MRI], biopsy, computerized axial tomography [CAT], bone scan, galactography, ultrasound), histological type (infiltrating carcinoma, infiltrating ductal carcinoma, infiltrating lobular carcinoma, mucinous carcinoma, metaplastic carcinoma, intraductal carcinoma, and others) and serum marker levels (CA15-3, CA27.9, CEA, CA125).*Related to neoadjuvant treatment:* chemotherapy (regimen and whether it is completed), radiotherapy, hormone treatment, anti-HER2, and other therapies; and clinical and radiological response (assessed by MRI) categorized as no response (no changes or progression), weak partial response (if the tumor size reduced less than 50%), strong partial response (if the tumor size reduced by 50% or more), and complete response (no residual tumor) [17].*Related to surgery*: date, duration of the intervention, emergency vs scheduled, surgical technique (quadrantectomy, lumpectomy, segmentectomy, simple mastectomy, radical mastectomy, modified radical mastectomy, skin-sparing mastectomy, nipple-sparing mastectomy, contralateral prophylactic mastectomy, lymphadenectomy), time between diagnosis and intervention and/or pre-surgical adjuvant treatment, and intraoperative complications (bleeding, nerve injury, anesthetic complications, allergic reaction to the prophylactic antibiotic, others).*Related to anatomical pathology*: laterality, sentinel node biopsy (yes/no and results), histological type (intraductal, ductal, lobular, tubular, mucinous, medullary, cribriform, papillary, non-specific, others), degree of differentiation, pathological TNM (pTNM), location, size, distant metastases, vascular and nervous infiltration, number of lymph nodes analyzed and number positive, margin involvement, estrogen receptor/progesterone receptor status, Ki-67, P53, CK5/6, CK14, CK19, and HER2 expression, oncotype, and MammaPrint.*Related to admission*: setting (hospitalization vs. or ambulatory surgery), length of hospital stay in days after first intervention, in-hospital complications (seroma, wound infection, necrosis of skin flap, pneumothorax, brachial plexus pathology, and others), reintervention during admission, other medical treatments, and death.*Related to follow-up*: primary treatment: adjuvant postoperative treatment (radiotherapy, chemotherapy, hormone therapy, anti-HER2, and other therapy), date of treatments, reconstructive plastic surgery (yes/no, technique and date), other postoperative treatments (rehabilitation, psychologist/psychiatrist, others), and contact with social services; immediate complications and any reported during the follow-up period: chest wall and breast complications (seroma, post-surgery adhesions, soft tissue necrosis and recurrent skin infections), musculoskeletal (reduced arm mobility), lymphedema, neurological (paresthesias, neuropathy, cognitive dysfunction), pulmonary (pneumonitis, pulmonary fibrosis) cardiovascular morbidity (cardiomyopathy), psychological effects (anxiety), pain, other toxicities (ototoxicity, nephrotoxicity), reproductive health (premature menopause, infertility, sexual dysfunction), osteoporosis, weight gain, mycosis, and immunosuppression (agranulocytosis, lymphopenia); complications after reconstructive surgery (prosthesis infection, capsular contracture, others) and reinterventions, readmissions, death and their respective causes; and management of the disease during the follow-up period: diagnostic tests after surgery (CAT, positron emission tomography-CAT, biopsy, MRI, others), treatments (surgery, radiotherapy, chemotherapy, hormone therapy, anti-HER2, others), and number of follow-up visits per year (to the surgery/gynecology department, oncology department, rehabilitation unit, pain unit and palliative care unit).
*- Patient-reported measures*

The EORTC-QLQ-C30 (version 3.0) [18, 19] is an internationally validated health-related quality of life questionnaire that is widely used in cancer research. The core questionnaire is comprised of 30 items that assess five functioning domains (physical, role, cognitive, emotional, and social); eight cancer symptom domains (fatigue, pain, nausea and vomiting, dyspnea, insomnia, appetite loss, constipation, and diarrhea); financial difficulties, and global quality of life. The scores are transformed to a 0-100 scale, with a high score implying a high level of functioning or global quality of life, while for the symptom domains, higher scores indicate greater symptom burden. In conjunction with this core questionnaire (QLQ-C30), the breast cancer specific module, EORTC-QLQ-BR23, will be used [20]. This consists of 23 items assessing disease symptoms, side effects of treatment (surgery, chemotherapy, radiotherapy and hormonal treatment), body image, sexual functioning, and future perspectives. The scoring approach is identical to that for the QLQ-C30.

The self-complete version of the EuroQol generic health-related quality of life questionnaire (EQ-5D) [21] consists of two parts: the EQ-5D-5 L descriptive system and the EQ Visual Analogue scale (EQ VAS). The descriptive system comprises five dimensions (mobility, self-care, usual activities, pain/discomfort and anxiety/depression). Each dimension has five answer options that define different levels of severity. The EQ VAS records respondent’s self-rated health on a 20-mm vertical, visual analogue scale, ranging from 0 (worst imaginable health state) to 100 (best imaginable health state).

The HADS [22, 23] is a 14-item measure that evaluates psychological status. Seven items evaluate depression (the HADS-D subscale) and seven evaluate anxiety (the HADS-A subscale). A subscale score of 0 to 7 indicates the absence of anxiety or depression; 8 to10 a possible case of anxiety or depression; and 11 or higher a probable case of anxiety or depression.2.Outcomes:- Objective outcomes: Second primary malignancies, complications, recurrence (local, regional, or remote), and death.- Patient-reported outcomes: Changes in the EORTC-QLQ-C30, EORTC-QLQ-BR23, HADS and EQ-5D-5 L scores between the time of inclusion in the study and the follow-up, initially at 2 years and then at 5 years.

